#### Tertiary outcome measures

Trunk Impairment Scale (TIS) and Barthel Index (BI), assessing trunk control and ADL, will be used as tertiary outcome measures. The TIS consists of three subscales assessing both static and dynamic sitting balance as well as trunk coordination. TIS scores range from a minimum of 0 to a maximum of 23; subscales score up to 7, 10, and 6 points, respectively. A higher score indicates better truncal function. The static sitting balance subscale assesses whether a person can sit independently and remain seated with their legs crossed. The dynamic sitting balance subscale assesses the ability to actively shorten each side of the trunk, initiated from either the shoulder girdle or the pelvic girdle. The trunk coordination subscale assesses the ability to rotate the shoulder girdle and the pelvic girdle [15]. Reliability, validity, and internal consistency of the TIS for stroke patients have been reported (ICC = 0.96; TIS-TCT *ρ* = 0.84; Cronbach’s *α* = 0.89) [1, 15, 40]. The BI is an index assessing the independency of a patient’s performance concerning the ADL. The maximum score of the BI gives a score out of 100 with increments of 5 points to assess whether the patient is fully dependent, independent, or needs some help regarding ten topics: feeding, bathing, grooming, dressing, toilet use, bowel and bladder continence, transferring, mobility, and stair climbing [41]. Reliability, validity, and internal consistency of the BI have been reported (ICC = 0.94; BI-FIMmotor *r* ≥ 0.92; *α* = 0.89–0.90) [42, 43]. Table 2 summarizes all the outcome measures described herein.

**Table 2 Tab2:** Outline of the outcome measures

Outcome measure	Domain	Tool	Baseline	Post	Follow-up
Eligibility assessment					
FAC	Gait	Clinical	X		
Primary outcome measure					
Tinetti Test	Gait	Clinical	X	X	X
Secondary outcome measures					
% stance, % swing	Gait	Biomechanical, spatiotemporal	X	X	X
% SS, % DS	Gait	Biomechanical, spatiotemporal	X	X	X
Stride time	Gait	Biomechanical, spatiotemporal	X	X	X
Stride length	Gait	Biomechanical, spatiotemporal	X	X	X
Step time	Gait	Biomechanical, spatiotemporal	X	X	X
Step length	Gait	Biomechanical, spatiotemporal	X	X	X
Step width	Gait	Biomechanical, spatiotemporal	X	X	X
Walking speed	Gait	Biomechanical, spatiotemporal	X	X	X
Cadence	Gait	Biomechanical, spatiotemporal	X	X	X
ROM trunk	Gait	Biomechanical, kinematics	X	X	X
Displacements trunk	Gait	Biomechanical, kinematics	X	X	X
Displacements COM	Gait	Biomechanical, kinematics	X	X	X
Normalized integrated linear envelope of the EMG signal	Gait	Biomechanical, EMG	X	X	X
Tertiary outcome measures					
TIS	Trunk	Clinical	X	X	X
Barthel Index	ADL	Clinical	X	X	X

*FAC* Functional Ambulation Categories, *SS* single support, *DS* double support, *ROM* range of motion, *COM* center of mass, *EMG* electromyography, *TIS* Trunk Impairment Scale, *ADL* activities of daily living

### Sample size

Analysis was based on results of a previous randomized controlled trial concerning the effect of additional trunk exercises on the TT and TIS that was carried out by our research group [7]. Saeys et al. (2012) [7] reported a change score of the TT of 13.45 and 5.2 points for the experimental and control groups, respectively. The number of patients required for this study was calculated a priori to ensure sufficient statistical power. Analysis showed that a sample size of 30 patients in each group, 60 in total, was necessary to detect a difference with 80% using a two-tailed hypothesis (with significance level of *p* = 0.05).

### Statistical analysis

Descriptive data analysis will be performed for the collected variables of the participants. The Kolmogorov-Smirnov Test and visual inspection of the data will be performed to evaluate whether the data are normally distributed. Differences between the experimental and control groups for the clinical data will be evaluated by means of repeated measures (ANOVA). Level of significance will be set at *p* < 0.05. When the stroke population is too heterogeneous, stratified sampling will be done to divide the study population into more homogenous groups. Differences along the entire kinematic, kinetics, and EMG curves will be assessed by means of spm1d in MATLAB®. Statistical parametric mapping will make interference about the topological features of statistical processes that are continuous functions [44].

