#### Post-treatment assessment and follow-up

Immediately after the intervention and 1 month post intervention, patients will again be subjected to a clinical and biomechanical assessment to examine treatment effect and the treatment effect sustainability.

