#### Discontinuations

Patients who withdraw from the study prior to intervention and after giving consent will be reported as “did not receive intervention.” If they withdraw during the 4-week intervention phase, an intention-to-threat analysis will be performed. Analysis will be performed as if the subject received the treatment (or control condition). Reasons for withdrawal will be noted.

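### The Tinetti analysis names no tested term, primary visit or baseline adjustment; a baseline-adjusted post-treatment contrast would answer the primary objective more directly at no cost

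*Protocol article*

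**What the plan says.** The Statistical analysis section of the protocol article gives one sentence on the test for the clinical scales: "Differences between the experimental and control groups for the clinical data will be evaluated by means of repeated measures (ANOVA". It adds "Level of significance will be set at *p* < 0.05". It does not say whether the group main effect, the group-by-time interaction or a contrast at one visit is the test, and it mentions no baseline covariate.

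Table 2 schedules the TT at baseline, post-treatment and follow-up. Post-treatment assessment and follow-up states: "Immediately after the intervention and 1 month post intervention, patients will again be subjected to a clinical and biomechanical assessment". It links these assessments to the treatment effect and to whether that effect lasts. The Objectives section makes the same split: the effect on gait performance is the primary objective and sustainability the second. The Primary outcome measures section names the TT without a visit, and gives its maximum as 28 points and its minimal clinically important difference (MCID) as 7 points.

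The Sample size section rests on a previous trial that "reported a change score of the TT of 13.45 and 5.2 points for the experimental and control groups, respectively". It concludes that "a sample size of 30 patients in each group, 60 in total" "was necessary to detect a difference with 80% using a two-tailed hypothesis". It gives no SD and no correlation between visits.

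**The concern.** The primary objective asks one question: how many TT points separate the groups at the end of the 4-week programme. A three-visit repeated-measures ANOVA supplies two omnibus tests involving group, and neither asks exactly that.

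- **Group main effect.** This compares patient means over all three visits. One visit precedes treatment, and randomisation makes the expected difference there zero, so the contrast is diluted.
- **Group-by-time interaction.** This asks, on 2 degrees of freedom, whether the group difference changes anywhere over the three visits. It is not tied to a visit and yields no number of points. Its result also depends on what happens at 1 month, which the protocol treats as a separate and open question.

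At stake are the chance of detecting a real end-of-treatment effect, and whether the main result is a difference in points that can be set beside the MCID. The baseline TT, which could sharpen the comparison, is already scheduled.

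**Working it through.** **The plan's own figure.** The difference in change scores is 13.45 − 5.2 = 8.25 points. Without an SD, the 30 per group cannot be reproduced, only solved backwards. A two-sided 5% t-test with 30 per group has 80% power at a standardised difference of 0.7356, which implies an SD of change of 8.25 / 0.7356 ≈ 11.2 points. The comparison below needs only the standardised value.

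**Inputs.** From the article: n = 30 per group, two-sided 0.05, three TT visits, 80% power on a change-score difference. Assumed: compound symmetry, a between-visit correlation ρ of 0.5, 0.7 or 0.8, and no missing data.

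**Set-up.** Let the SD of change be 1, so one TT measurement has variance σ² = 1 / [2(1 − ρ)]. Let d = 0.7356 be the effect at end of treatment. The noncentrality of the change-score test is (n/2)d² = 15 × 0.5411 = 8.12, which gives 80% on 1 and 58 df.

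**Group main effect, sustained effect (0, d, d).** The mean effect is 2d/3 and the variance of a patient's mean is σ²(1 + 2ρ)/3. The noncentrality is therefore 8.12 × (8/3)(1 − ρ)/(1 + 2ρ):
- ρ = 0.5: 8.12 × 0.667 = 5.41
- ρ = 0.7: 8.12 × 0.333 = 2.71
- ρ = 0.8: 8.12 × 0.205 = 1.67

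**Group-by-time, 2 and 116 df.** The noncentrality is (n/2) × Σ(centred effects)² / [σ²(1 − ρ)]. Since σ²(1 − ρ) = 1/2, ρ drops out.
- Sustained (0, d, d): Σ = (2/3)d², noncentrality 15 × (2/3) × 0.5411 × 2 = 10.82
- Halved at 1 month (0, d, d/2): Σ = 0.5d², noncentrality 15 × 0.5 × 0.5411 × 2 = 8.12, now spread over 2 df

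**Baseline-adjusted contrast at end of treatment (ANCOVA), 1 and 57 df.** The residual variance is σ²(1 − ρ²), so the noncentrality is 8.12 × 2/(1 + ρ): 10.82, 9.55 and 9.02.

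| Test | ρ = 0.5 | ρ = 0.7 | ρ = 0.8 |
|---|---|---|---|
| Change score, end of treatment (anchor) | 80% | 80% | 80% |
| Group main effect, sustained | 63% | 37% | 25% |
| Group main effect, halved at 1 month | 40% | 23% | 16% |
| Group-by-time, sustained | 84% | 84% | 84% |
| Group-by-time, halved at 1 month | 71% | 71% | 71% |
| ANCOVA, end of treatment, either pattern | 90% | 86% | 84% |

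At ρ = 0.3 the ANCOVA has 94% and the sustained group main effect 86%. At ρ = 0.9 they have 82% and 14%. A simulation of 3,000 trials per setting at the three tabulated correlations agreed with the table. It put the type I error of all four tests between 4.3% and 5.8%.

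**The case against.** A reader might infer that the plan tests the wrong contrast and that the trial's power is as low as 25%. The documents do not support this. The article names no ANOVA term, and the low figures apply only to the group main effect. With baseline as one of the repeated measurements, group-by-time is the usual term of interest, and it compares changes from baseline. With baseline and post-treatment alone it would equal the change-score test, so the sizing basis is compatible with it. An additive chance imbalance at baseline cancels from it.

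Nor can a general loss of power be claimed. With a sustained effect the interaction (84%) exceeds the change-score anchor. It is about 2 points below ANCOVA at ρ = 0.7, level at 0.8 and slightly above at 0.9. The 71% arises when the effect halves; if the effect vanished completely by 1 month, the interaction would again have 84%. Dilution of the main effect to two thirds presumes that the effect does not grow: with effects 0, d and 1.5d the average is 2.5d/3 = 0.83d.

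It can also be said that the objectives already imply the post-treatment visit as primary, that covariates and covariance structure are commonly left to an analysis plan or full protocol, and that repeated-measures ANOVA does not prevent visit-specific estimates from being reported.

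All of this stands as a limit on the claim. It does not remove the case for change. The article does state its method, the stated method leaves the primary contrast open, and a more direct one is available from data already scheduled.

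**Conclusion.** The point holds as an improvement to a valid analysis. The plan ties the TT comparison to no term, visit or baseline adjustment, although it separates treatment effect from sustainability and sizes the trial on a change score.

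The baseline-adjusted end-of-treatment contrast has about 90%, 86% and 84% power at correlations of 0.5, 0.7 and 0.8, and these figures do not depend on the follow-up visit. Against the group main effect with a sustained effect, the advantage is large: 27, 49 and 59 percentage points. Against group-by-time it is about 19, 15 and 13 points if the effect halves by 1 month. If the effect is fully sustained it is about 6 and 2 points at correlations of 0.5 and 0.7, and nil at 0.8. The gain that does not depend on these assumptions is interpretive: a difference in points at a named visit.

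The power figures rest on compound symmetry, the assumed correlations, complete data and the 80% anchor. The article supplies no SD or correlation with which to narrow them.

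**What to change.** In Primary outcome measures, name the TT total immediately after the intervention as the primary endpoint. In Statistical analysis, make the primary analysis the between-group difference at that visit adjusted for baseline TT. Use either ANCOVA or a mixed model with baseline TT as covariate and terms for visit, group and group-by-visit. Report the difference in points with a 95% confidence interval beside the 7-point MCID. Take the 1-month difference from the same model as the secondary analysis of sustainability; with ANCOVA, fit the same form to the 1-month score. In Sample size, say that the calculation refers to the end-of-treatment difference and supply the SD used.

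The cost is wording in the statistical sections. No patient, visit or measurement is added, because Table 2 already schedules the TT at baseline and both later visits. Recruitment was still under way, with 28 of 60 patients, according to Current study status; the change should be made and dated before any outcome is compared by group.

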### Data collection and management

Standardized forms have been drafted to ensure accurate and reliable data collection regarding clinical information and assessment. Furthermore, multiple training sessions will be provided to the assessors and therapists to ensure standardized treatment, assessment, and data analysis. The amount of training will be dependent on the familiarization with the clinical scales and therapy techniques of the assessors and therapists. Standardized procedures have to be followed during assessment and treatment. Several meetings will be held where the primary investigator will be informed about current affairs and can be consulted if questions arise or problems occur. Collected data and information will be processed with the utmost discretion and anonymity; patient data will be registered by means of an identification number and not by name. The primary investigator will keep records of the patients’ clinical records and data, so patients can be contacted for follow-up assessment if they are already discharged. Patient records and data will be kept for 10 years after publication as suggested by the Ethics Review Committee of the University Hospital of Antwerp (UZA, Edegem, Antwerp, Belgium).

### Ethical considerations and dissemination

#### Ethics review

Ethical approval of the study has been obtained from the Ethics Review Committee of the University Hospital of Antwerp (UZA, Edegem, Antwerp, Belgium) and the Ethics Review Committee of the GasthuisZusters Hospital (GZA, Wilrijk, Antwerp, Belgium). The following reference numbers were used during the application: 15/42/433 and 151203ACADEM. The trial is registered in the electronic database for clinical trials (ClinicalTrials.gov; 2 March 2016; ID: NCT02708888).

#### Safety

Although we foresee no major risks or adverse effects, patients who are harmed during the course of this study will receive no compensation since treatment and assessment are applied as a health care service provided under national health insurance. If harm is caused by therapists or assessors, the appropriate insurance will cover the expenses.

#### Dissemination

The results of this study will be presented at several research conferences, published in peer-review journals, and will be included in the doctoral thesis of the primary investigator. Findings will be presented at several workshops and training days for practicing physiotherapists hosted by the University of Antwerp and located in several rehabilitation hospitals such as RevArte, care and nursing facilities.

## Discussion

The aim of this study is to further explore the effects of additional customized trunk exercises on clinical and biomechanical gait performance. Despite the evidence demonstrating the importance of trunk control after stroke, studies about the effects of trunk rehabilitation on gait performance are inconsistent. The findings of this study might lead to new scientific insights into the importance of the trunk during gait rehabilitation in people suffering from stroke submitted to a rehabilitation hospital. Since clinical improvements are of greater importance to patients and physiotherapists as they assess functional tasks and are easier to use in a clinical setting, the TT and its subscales will be the primary outcome measures. Subsequently, a variety of biomechanical parameters collected by a full body gait analysis will be our secondary outcome measures. However, it is still important to consider the effect of this training program on the trunk itself and on ADL as this is the main focus of the training program. Because of this, the TIS and BI will assessed as tertiary outcome measures.

Our trial has several strengths. Firstly, since both clinical and biomechanical outcome measures will be examined, it is of interest to take a closer look at the relationship between both assessment methods. Several biomechanical parameters, such as step symmetry, step width, and step length, are assessed by the TT. Investigating whether the clinically observed parameters are significantly different from the biomechanical parameters assessed in a gait laboratory might reveal whether these tests are sufficient to tell us something about gait performance. In addition, the TIS evaluates trunk control in a seated position. With the results of this study, it is possible to examine whether the TIS is able to predict trunk motion during walking. Secondly, a more sophisticated treatment protocol based on new scientific insights and a previous study within our research group will be used to enlarge therapeutic improvements [7]. The following important changes will be implemented in this training protocol: (1) a more intensive exercise program as it is hypothesized that a high dose of task-specific exercises should be applied over a short period of time. Therefore, both groups will receive additional therapy for 1 h a day, 4 days a week over a short period of 4 weeks, (2) this is an exercise program that is executed on unstable surfaces since Karthikbabu et al. (2011) reported short-term effects in favor of exercises on physio balls compared to plinth training [45]. Thirdly, the investigation of the sustainability of the effects of trunk exercises over time. It is important to know whether the treatment effects are sustainable over time or if continuous therapeutic input is necessary to maintain the level of functioning even after patients are discharged home. Lastly, the effect of trunk rehabilitation on biomechanical parameters has not yet been thoroughly examined.

However, there are a few limitations to consider. Blinding of therapists and patients will be unfeasible as the experimental and control therapies differ considerably. Subsequently, to our knowledge no research has been conducted to examine the effect of cognitive exercises on measures of balance and gait. Although, we assume that the control therapy will not reveal carry-over effects on balance an gait, we cannot say this without doubt. However, the exercises are drafted in a way that no carry-over will be expected. In addition, trunk exercises do not solely activate trunk muscles. Lower limb muscles will also be activated during seated reaching exercises [31]. It is almost impossible to eliminate lower limb activity during motor activities. Yet, the specificity of the training program concerns trunk control and activation of the upper and lower trunk.

After completion of this study we will have gained insights into the effects of trunk rehabilitation on clinical and biomechanical parameters of gait performance. This protocol was written according to the SPIRIT 2013 Statement [45]. The SPIRIT Checklist can be found as an additional file (see Additional file 1).

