### Objectives

The primary objective of this study is to examine the effect of an additional trunk exercise program on gait performance after stroke. Primarily, clinical assessment of gait performance is made by the Tinetti Test (TT) and its subscales; secondarily, biomechanical assessment by a full body gait analysis. Trunk performance will be assessed by means of the Trunk Impairment Scale (TIS) and the independency of a patient’s performance concerning activities of daily living (ADL) by the Barthel Index (BI). Patients suffering from stroke will be receiving either 16 h of additional trunk exercises or the same duration of cognitive exercises for a period of 4 weeks.

The second objective is to explore the sustainability of the effects of trunk exercises over time. It is important to know whether the treatment effects are sustainable over time or if continuous therapeutic input is necessary to maintain the level of functioning even after patients are discharged home.

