### Outcome measures

#### Primary outcome measures

Gait performance as measured clinically via the TT is the primary outcome measure. The FAC will not be used as an outcome measure to assess gait performance as it is a more descriptive clinical measure and less detailed compared to the TT. The TT measures gait and balance using a 2- or 3-point ordinal scale with scores ranging from 0 to 1 or 2. The maximum score of the total TT is 28 points, whereby a maximum of 12 and 16 points can be obtained for gait and balance subscales, respectively. Nine items, such as sit to stand, standing balance with eyes open and eyes closed, turning 360° and sitting down, are assessed on the balance subscale. The gait subscales assess eight items ranging from step length, step symmetry, foot clearance, and step width. Reliability and validity of the TT for stroke patients have been reported (ICC2,1 = 0.84; TT-FIMmotor *r* = 0.55; TT-gait speed *r* = 0.82) [39]. The minimal clinically important difference of the TT is 7 points (area under the curve (AUC) = 0.743) and a minimal detectable change of 6 points [39].

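### The article does not settle whether the primary outcome is the Tinetti total alone or the total with its two subscales, and the total it labels as gait is 57% balance points

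*Protocol article*

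**What the plan says.** The protocol article defines the primary outcome in two ways.

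- **Three scores.** Objectives: "Primarily, clinical assessment of gait performance is made by the Tinetti Test (TT) and its subscales". Discussion: "the TT and its subscales will be the primary outcome measures".
- **One score.** Primary outcome measures: "Gait performance as measured clinically via the TT is the primary outcome measure". Table 2 has a single primary row, "Tinetti Test Gait Clinical X X X", and no row for a subscale. The Sample size section uses only TT change scores, 13.45 against 5.2 points.

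On the content of the scale, Primary outcome measures says: "The maximum score of the total TT is 28 points, whereby a maximum of 12 and 16 points can be obtained for gait and balance". The same section gives a minimal clinically important difference (MCID) of 7 points for the TT.

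On timing, Post-treatment assessment and follow-up says: "Immediately after the intervention and 1 month post intervention, patients will again be subjected to a clinical and biomechanical assessment". The Objectives place sustainability over time under a second objective. The Statistical analysis section plans repeated measures ANOVA for the clinical data and adds "Level of significance will be set at" p < 0.05. It does not say which effect of that ANOVA, or which visit, decides the primary question.

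**The concern.** Two separate problems follow.

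First, a reader cannot tell whether one score or three can make the trial positive. Under the three-score wording, with one common threshold and no statement of which score counts, a claim resting on whichever score is significant carries more than a 5% false-positive risk. The choice between the two wordings could also be made after the results are seen.

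Second, the objective is gait performance, but the total mixes gait with balance. The Background reports that trunk programmes already appeared to help sitting and standing balance, and that their effect on gait still needs confirming. The total therefore pools the component where benefit is expected with the component the trial was set up to test. A significant total would not show which of the two moved.

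**Working it through.** **Inputs from the article:** gait maximum 12, balance maximum 16, total 28; MCID 7; TT changes 13.45 and 5.2; 30 per group; two-sided 0.05; 80% power; two post-baseline visits.

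**Assumed, because the article does not give them:** normally distributed scores; subscale SDs in the ratio 12:16; correlation between subscales 0 to 0.9; correlation between visits 0.5 to 0.9 (0.6 in the ANOVA runs).

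**1. The planning figure.** The difference is 13.45 − 5.2 = 8.25 points on the TT. No SD is stated, so 30 per group can be neither confirmed nor refuted. It implies SD = 8.25 / [(1.960 + 0.842) × √(2/30)] = 11.4. This is a TT-total calculation, and nothing comparable is given for either subscale.

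**2. Familywise error if any one score may carry the claim.** Three independent tests would give 1 − 0.95³ = 14.3%. The scores are not independent, because the total is the sum of the other two. Null trials were therefore simulated with 30 per group and total = gait + balance (40,000 per scenario; 20,000 for the ANOVA column):

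| Subscale correlation | Three scores, one visit | Three scores, one group-by-time test each | Three scores, each visit tested separately |
|---|---|---|---|
| 0 | 11.3–11.5% | 11.4% | 15.8–19.8% |
| 0.3 | 10.4–10.6% | 10.6% | 14.6–18.5% |
| 0.5 | 9.4–9.9% | 9.8% | 13.4–16.6% |
| 0.7 | 8.6–8.9% | 8.9% | 12.0–15.5% |
| 0.9 | 6.9–7.0% | 7.2% | 9.7–12.7% |

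With the TT total alone and one group-by-time test, the simulated error was 4.7–5.3%, that is, the nominal 5%. The last column describes a plan that the article does not state.

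**3. What the total measures.** The balance share is 16/28 = 57.1% and the gait share 12/28 = 42.9%. Since total = gait + balance, a between-group difference of 0 on gait and 8.25 on balance gives 8.25 on the total, exactly the planning difference. Both 7 and 8.25 are below the balance maximum of 16, so either can be reached with no change on a gait item. In addition, the earlier trial's experimental-arm change of 13.45 exceeds the gait maximum of 12. At least 13.45 − 12 = 1.45 points of it must have come from balance.

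**The case against.** The sections that formally define the outcome and the sample size favour one score, and on that reading the multiplicity between scores disappears. This is a fair account of where the weight lies. It does not remove the conflict, because the Objectives and the Discussion say otherwise and nothing ranks one statement above the other.

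Multiplicity rules commonly sit in an analysis plan, which is not shown here. That also stands: the absence of an adjustment is not the point. The contradiction is in the article itself, and a later plan could follow only one of its two definitions.

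A reader might infer six chances at 0.05, three scores at each of two visits, with an error of about 10–20%. The documents do not support this. The stated method is repeated measures ANOVA, where one group-by-time test per score covers both visits, and sustainability belongs to the second objective. It is also an assumption that any one significant score would count as success.

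On content, the article reports a correlation of 0.82 between the TT and gait speed, discloses the 12/16 split, and measures gait directly in the laboratory as secondary outcomes. A balance-only effect would therefore be visible to a careful reader. However, the correlation does not show which items produce a between-group difference, and the secondary outcomes do not limit what may be concluded from the primary one. It is true that a 7-point balance gain needs at least 7 points of room at baseline, and no baseline scores are given. The argument shows what is possible on the scale, not what is likely.

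**Conclusion.** The point holds in two parts.

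- **Contradiction.** The article gives two definitions of the primary outcome. If any one of the three scores may carry the claim, familywise error is about 7–11% instead of 5%, whether tested at one visit or by one group-by-time test per score. The range rests on the assumed correlations and SD ratio. If the TT total alone is primary, with one named test, error is 5%.
- **Interpretation.** The total assigned to the gait domain is 57% balance points. A balance-only effect of the size of the MCID or the planning difference could be concluded as improved gait. This part is scale arithmetic and needs no assumption about SDs or correlations. Correcting alpha would not cure it.

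Both matter because they decide which score makes the trial positive and whether a positive result answers the stated question.

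**What to change.** Make the Objectives, Primary outcome measures, Table 2 and Discussion agree on the following.

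1. **One primary endpoint:** the TT total, described as gait and balance, with one named test. That test is either the group-by-time effect or the between-group contrast at the post-treatment visit.
2. **Fixed order at two-sided 0.05:** TT total, then gait subscale, then balance subscale, stopping at the first non-significant result. The 1-month visit stays under the second objective.
3. **Rule for the conclusion:** improved gait performance is claimed only if the gait subscale also shows a benefit.

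This holds familywise error at 5% and leaves the 30 per group as it is. Splitting alpha equally over three scores (0.0167 each) would cost more. If, purely for illustration, 8.25 and SD 11.4 are applied to each score, power at 30 per group falls from 80% to about 66%, and 41 per group would be needed.

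The costs should be stated openly. The subscales lose independent 5% tests. The gait subscale has no stated power, because 8.25 is a TT-total difference. A real gait effect diluted by unchanged balance items could leave the total non-significant and would then not be formally tested. If the sponsor finds that unacceptable, the alternative is to make the gait subscale primary and redo the sample size on it.

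The change is one of wording. The article reports 28 patients already recruited and a primary investigator who knows allocation, so the amendment should be dated and made before outcomes are examined by group.
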